In 2012 the Metro South Addiction and Mental Health Service (MSAMHS) opened the first of three planned CCUs in the inner suburb of Coorparoo, in the city of Brisbane, Australia (see Table 1). Two more units have been opened in the outer-suburbs of Bayside and Logan in 2014/2015. All three services provide independent living units with the availability of 24-h staff support. The Coorparoo unit has a traditional clinical staffing model with a manager, occupational therapist, psychologist, social worker, nursing and medical staff (a ‘clinical staffing model’). The staffing at Bayside and Logan involves collaboration between clinical staff and peer workers (an ‘integrated staffing model’) [19]. Under the integrated model, peer workers replace non-senior nursing roles with the responsibility for implementing individualised rehabilitation plans for consumers. Peer workers comprise 61 % and 56 % of full-time equivalent staff at the Bayside and Logan CCU sites respectively. Unique features of the integrated model are the direct collaboration between peer workers and clinical staff within a single team, and peer support workers fulfilling the role of principal support or case manager in the day-to-day delivery of care.

**Table 1 Tab1:** Characteristics of the Coorparoo, Bayside and Logan CCUs, and their referring districts

			Coorparoo CCU	Bayside CCU	Logan CCU
Location		Distance from state capital (km)	4.2	30.9	21.2
		LGA Index of Relative Socio-economic Disadvantage, 2011^a^ [85]	90	83	46
Referring district		Population [86]	588,475	143,628	287,517
		Availability of acute inpatient services	Yes	Yes	Yes
		Availability of community mental services	Yes	Yes	Yes
		Availability of inpatient rehabilitation mental health beds	No	Yes	No
		Availability of transitional housing team	Yes	No	No
		Availability of community based non-residential rehabilitation team	Yes	No	Yes
		Availability of dedicated mental health homelessness team	Yes	No	Yes
CCU	Philosophy of care	Recovery-oriented	Yes	Yes	Yes
		Strengths-based	Yes	Yes	Yes
		Designated rehabilitation focus	Yes	Yes	Yes
		Voluntary engagement in rehabilitation^b^	Yes	Yes	Yes
		Individualised care planning	Yes	Yes	Yes
		Transitional support	Yes	Yes	Yes
		Role of peer support in care planning and delivery	Limited	Focussed	Focussed
	Physical environment	Maximum occupancy (consumers)	20	20	16
		Number of self-contained independent living units	20	20	15
		Number of disabled access units	1/20	1/20	1/15

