		Shared recreation and leisure facilities	Yes	Yes	Yes
	Available treatment & support	Individual psychotherapy support (CBT)	Yes	Yes	Yes
		Living skills support and development	Yes	Yes	Yes
		Structured leisure and physical activities	Yes	Yes	Yes
		Evidence based therapeutic group programmes	Yes	Yes	Yes
	Staffing	Staffing model	Clinical	Integrated	Integrated
		Total FTE staff	21.5	24.5	18.4
		Total FTE peer-support staff	0.6	16	10.4
		Total FTE clinical staff	19.9	7.5	7
		Peer support : Clinical staff ratio	0.03	2.13	1.49
		Staff : Consumer ratio	1.08	1.23	1.15

^a^Local Government Area (LGA) percentile rank of Relative Socio-economic Disadvantage in comparison to all other LGAs in Australia

^b^Involuntary consumers are accepted at all three CCUs with explicit emphasis on voluntary engagement in available rehabilitation activities

There is an expectation that similar care will be delivered across the CCUs operating the integrated and clinical staffing models. The processes for staff orientation and training at the Bayside and Logan sites were modelled from those initially implemented at the Coorparoo CCU. All three of the MSAMHS CCUs operate under a common state-wide model of service [22] and have a shared governance structure. The key distinction between these sites is their staffing models and geographic locations (see Table 1). The current iteration of the model of service emphasises provision of recovery oriented rehabilitation and support to consumers with severe and persistent mental illness to assist them towards personal recovery. Definitions of recovery and recovery-oriented practice in these services are taken from The National Framework for Recovery-oriented Mental Health Service (NFROMHS) [25]. This framework defines recovery oriented practice as that which:“Recognises and embraces the possibilities for recovery and wellbeing created by the inherent strength and capacity of all people experiencing mental health issuesMaximises self-determination and self-management of mental health and wellbeingAssists families to understand the challenges and opportunities arising from their family member’s experiences (p3).”

The concept of personal recovery is defined under the framework as: “being able to create and live a meaningful and contributing life in a community of choice with or without the presence of mental health issues” (p2).

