### Aims and benefits

The study examines the outcomes of engagement with CCUs, and considers the impact of the integrated staffing model on both the outcomes and experiences of care in comparison to a clinically staffed CCU.

The quantitative component of the study explores the expectation that consumers under integrated and clinical staffing models will experience improvement in psychosocial functioning as measured by the total Health of the Nation Outcome Scale (HoNOS) [26] score following discharge from CCU care, and that no significant differences will emerge between the changes observed under each model. Equivalence testing rather than assessing for superiority or non-inferiority of the integrated staffing model is supported by:The operation of an identical model of service across both the clinical and integrated sites, hence the expectation that equivalent care will be delivered. If equivalent care was realised was a staffing model where the majority of staff are employed on the basis of their ‘lived experience’ rather than clinical expertise this would support future decision-making about staffing on the basis of secondary considerations [27] such as cost-effectiveness and consumer preference.Limitations in the quantitative evidence base relating to the impact of the integration of peer support to justify a hypothesis of superiority. Where quantitative findings are available these have tended to discuss equivalent outcomes to clinical staff. Furthermore, a failure to demonstrate superiority of the integrated model would not answer the question of whether such a staffing approach may be appropriate to be considered by other services [28].The limitations of testing a non-inferiority hypothesis with regards to establishing the equivalence of the two models where qualitative differences in the experience of care are theorised, and the impact of these on consumer outcomes is unknown.

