### Sample

The project is currently in progress. The cohort will comprise all consumers admitted to the three MSAMHS CCUs (Bayside, Coorparoo and Logan) between December 2014 and December 2017 who provide informed consent to participate. Baseline and follow-up data will be sourced from administrative datasets for the 12-month period prior to and following CCU admission and discharge respectively.

As the study takes a naturalistic observational design, the only defined inclusion criteria is acceptance for a trial of CCU based rehabilitation care. Each CCU provides a six-week assessment period to establish suitability for engagement under the model of service. Given this, consumers who are discharged prior to the conclusion of this assessment period will be excluded from the study. This exclusion criterion assists in ensuring that included participants are aligned with the model of service. This reflects a modified intention-to-treat approach [34], as participants will be included regardless of their mode of exit from the CCU (planned/unplanned (CCU initiated)/unplanned (consumer initiated).

Based on anticipated service throughput, with a median length of stay at the Coorparoo CCU of 0.9 years (inter-quartile range 0.50-1.8 years) at a point estimate in 2013, and assuming a 70 % response rate, it was expected that at least 60 consumers from the integrated staffing model and 40 from the clinical staffing model would agree to participate over the study period. This minimum sample likely reflects an under-estimate given 37 unique admissions occurred to the Coorparoo CCU in the 12-month period from July 2012. Additionally, since the opening of the Bayside and Logan CCUs 50 of the 63 consumers admitted across all three sites met the inclusion criteria (79.4 %) and 42 (84.0 %) of eligible consumers provided consent to participate.

The adequacy of the estimated minimum sample size was considered using the Epi Info™ StatCalc program [35] for unmatched or cross-sectional cohort studies. This minimum sample was estimated to provide greater than 80 % power to detect a 15 % difference in outcome on the primary outcome measure at the 95 % confidence interval using the Fleiss calculation. The acceptability of this power is supported by an emergent difference of 20 % in outcome HoNOS scores in a recent Australian study examining outcomes of a community residential service for similar consumers [36].

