### Planned secondary outcome measures and descriptive data

The complexity of outcome assessment in mental health service evaluation and the appropriateness of relying on multiple measures to capture the breadth of relevant domains is well recognised [45]. A routine assessment battery (see Tables 2 & 3) was developed, piloted and adapted at the Coorparoo CCU site in consultation with senior medical and allied health workers over the initial two years of operation (2012–2014). Considerations in the development of this battery included ease of administration, incorporation of multiple perspectives (staff, consumers and carers) and sufficient breadth to capture data on functional, social, cognitive, recovery and symptom related domains.

**Table 3 Tab3:** Completion of relevant measures and explanation of routine clinical assessment battery

		Responsible person for ensuring completion					
Domain	Measure	Occupational therapist	Principle service provider	Psychology`	Medical	Social work	Notes on assessment battery

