Planned secondary outcome measures will be derived from this assessment battery and routine administrative data sets. Secondary outcome assessment will specifically focus on mean changes in symptomatology (Brief Psychiatric Rating Scale (BPRS) [46] & Scale for the Assessment of Negative Symptoms (SANS) [47]), disability (Life Skills Profile-16 [48]), recovery orientation (Stages of Recovery Instrument (STORI-30) [49]), carer quality of life (Adult Carer Quality of Life (AC-QoL) [50]), emergency department presentations, psychiatric inpatient bed days, and psychological distress and wellbeing (MHI-38) [51]). For each of these secondary measures it is again hypothesised that no differences in mean change will emerge between the clinical and integrated staffing models.

Descriptive details of consumer characteristics and care experience will also be recorded. Relevant information will include: age at CCU commencement, gender, ethnicity, marital status, years of education, diagnosis, involuntary treatment order status, medication, length of stay, and the mode of exit from the CCU (planned/unplanned (consumer initiated)/unplanned CCU initiated).

Information about the operational costs under the integrated and clinical staffing models over the December 2014 - December 2017 period will be reported descriptively. Additional information about the operational experience under the integrated and clinical staffing models including staff retention and absences will also be reported. Estimates of the cost of ongoing service utilisation following CCU engagement based on ED Presentations and acute inpatient bed days in the 12-months post-CCU discharge will be calculated using the most recently available state-wide cost estimates.

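### The single cost window takes in the opening or early months of the integrated units but not the clinical unit's start-up, so staffing model is mixed with unit maturity

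*Protocol article*

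**What the plan says.** Under *Planned secondary outcome measures and descriptive data*, the article fixes one calendar window for both models: "operational costs under the integrated and clinical staffing models over the December 2014 - December 2017 period will be reported descriptively".

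The opening dates are under *Evaluation context*. In 2012 the service "opened the first of three planned CCUs in the inner suburb of Coorparoo"; this is the clinical unit. For the integrated model, "Two more units have been opened in the outer-suburbs of Bayside and Logan in 2014/2015". The assessment battery was piloted at Coorparoo "over the initial two years of operation (2012–2014").

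*Aims and benefits* lists the comparison of operating costs, marked as descriptive, among four quantitative questions that accompany the primary outcome. The same section argues that if equivalent care were achieved under the integrated model, "this would support future decision-making about staffing on the basis of secondary considerations", and gives cost-effectiveness and consumer preference as examples.

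The article states no start-up exclusion and no alignment of the units by time since opening for the cost figures.

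**The concern.** A new residential unit has costs that an established one does not: staff are recruited and trained, and places may stand empty while the unit fills. A calendar window that catches this phase in one arm only makes the cost contrast partly a contrast of unit age. Here the overlap is complete: both integrated units are the new ones, and the only clinical unit is the established one. A full-window figure cannot separate the two influences.

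Other parts of the article confirm that the study catches the start of the integrated units only. *Evaluation context* describes data gathering over several stages of introducing the new staffing model. Table 5 schedules staff interviews at commencement for Bayside and Logan but not for Coorparoo, and its footnote explains that the latter was already running when the study began.

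What is at stake is how a descriptive result is read. If outcomes are judged equivalent, service planners may look to cost, and a start-up effect could be mistaken for a property of the staffing model.

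**Working it through.** **Inputs from the article**
- Cost window: December 2014 to December 2017. This is 36 months, or 37 if both end months count in full.
- Openings: Coorparoo 2012; Bayside and Logan 2014/2015, months not given.
- Table 1, "Total FTE staff": 21.5 (Coorparoo), 24.5 (Bayside), 18.4 (Logan). Maximum occupancy: 20, 20 and 16 consumers.
- Unit costs, occupancy over time and the timing of recruitment or training costs are not stated. The fill-up times below are assumptions.

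**Step 1. Reproduce the stated staffing figures.** The article gives no cost figure. The nearest stated quantity is the staff-to-consumer ratio, which is FTE divided by maximum occupancy:
- Coorparoo 21.5/20 = 1.075 (stated 1.08)
- Bayside 24.5/20 = 1.225 (stated 1.23)
- Logan 18.4/16 = 1.150 (stated 1.15)

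All three reproduce. Pooled, the integrated units have (24.5 + 18.4)/(20 + 16) = 42.9/36 = 1.192 FTE per place against 1.075, a ratio of 1.11.

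**Step 2. Place the openings against the window.** Coorparoo's initial two years (2012–2014) lie essentially before December 2014. Bayside and Logan opened either shortly before the window or inside it. Early operation in the window therefore applies to the integrated model only.

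**Step 3. Illustrate the effect on cost per occupied bed-day.** Suppose a unit is open for M months of the window, carries full running cost from opening, and fills in a straight line over R months. Occupied months per place are M − R/2, so cost per occupied bed-day is inflated by M/(M − R/2) − 1. A flat 50% occupancy for R months loses the same R/2 and gives the same answer.

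| Opening (36-month window) | R = 3 | R = 6 | R = 12 |
|---|---|---|---|
| At start, M = 36 | 36/34.5 = 1.04 | 36/33 = 1.09 | 36/30 = 1.20 |
| 12 months in, M = 24 | 24/22.5 = 1.07 | 24/21 = 1.14 | 24/18 = 1.33 |

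With a 37-month window the first row becomes 37/35.5, 37/34 and 37/31, or 1.04, 1.09 and 1.19.

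**Step 4. The opposite pull.** If totals over the window are reported, a unit opening 12 months in contributes only 24/36 = 67% of a full window of cost. The same late opening that raises cost per occupied bed-day lowers total cost.

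**Step 5. Opening before the window.** If a unit opened 3 months before the window and filled over 6 months, the window catches only the second half of the fill. The shortfall then runs from 50% to 0 over 3 months, a loss of 0.75 months, and the inflation is 36/35.25 = 1.02. A unit already full by December 2014 would show no fill-up effect.

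**The case against.** The strongest defence is that the window is deliberate. It matches the cohort's admission period, so costs are contemporaneous across models and cover the care of the people studied. Dropping the fill-up months would leave out the cost of caring for consumers admitted during them. The item is descriptive, and no test or error rate depends on it. The only early-intake figure, "37 unique admissions occurred to the Coorparoo CCU in the 12-month period from July 2012", is not an occupancy figure, but for a 20-place unit it does not suggest slow filling. The Discussion also expects service delivery to change over time and warns of site-specific effects.

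Most of this stands. It is a good reason to keep the full-window figure and to treat the percentages as illustration only. It does not remove the imbalance, because the general caveats in the Discussion are not connected to the cost comparison.

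Four stronger readings are tempting, and the documents do not support them.
- A reader might infer that the integrated model is bound to look dearer. Steps 3 and 4 show pulls in opposite directions, and staffing that grew in step with occupancy would shrink the first.
- A reader might infer that both openings fall inside the window. A unit opened in 2014 may have opened before December.
- A reader might infer that the difference in size (36 places against 20) tilts the comparison. The article never says that raw totals will be compared, Table 1 gives what is needed to standardise, and a denominator is a detail an article may leave to a fuller plan.
- A reader might take this table to be the figure on which staffing decisions will rest. *Aims and benefits* names cost-effectiveness only as one general secondary consideration, and operating cost alone is not cost-effectiveness.

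**Conclusion.** The point holds in a limited form. Reported as written, the full-window comparison mixes staffing model with unit maturity, because start-up or early operation falls within the window for the integrated model only.

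The direction and size of the distortion cannot be established. The illustrative 4% to 20% rise in integrated cost per occupied bed-day assumes opening at the start of the window, full staffing from opening, and fill-up over 3 to 12 months (equivalently, 50% occupancy for that time). It would be smaller for a unit opened before December 2014. It would be larger for one opened well into the window, but that unit's total cost would be lower.

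The 11% pooled gap in FTE per place gives a sense of scale only. It counts posts rather than money, and peer workers replace non-senior nursing roles at costs the article does not state, so the true cost difference between the models is unknown even in sign.

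This is a minor improvement to a descriptive output and affects no inferential result.

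**What to change.** Keep the December 2014 to December 2017 figure. Beside it, report cost per occupied bed-day for each of the three units by time since opening. State in advance how long the start-up period is taken to be, and show its costs separately, so that the models can also be compared in established operation. Give each integrated unit's opening month, so that readers can see how much of the window is early operation.

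This needs running costs and occupied bed-days by unit and period; the article does not say whether these are already held in that form. The cost is a little extra tabulation and a shorter period for the established-operation figure. Because the full-window figure stays, the cost of care during fill-up is not lost.

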### Planned predictors for hierarchical linear regression modelling

A limited number of predictors of positive psychiatric rehabilitation outcome have been supported by the international literature over the past decade. These include: medication adherence [52, 53]; lower baseline disability scores [52]; family engagement with the program and provision of peer support/self-help [52]; increasing age [53, 54]; female sex [54]; being diagnosed with schizoaffective disorder rather than schizophrenia [55] or any disorder other than schizophrenia [52]; and having been engaged with formal education [52]. The contribution of two potentially relevant predictors, namely cognitive function and rehabilitation engagement had not been explored. Cognitive functioning has emerged as a strong predictor in the vocational rehabilitation literature [56] as well as of functional outcomes in schizophrenia generally [57]. There has also been discussion about the importance of considering consumer engagement as a factor in rehabilitation outcomes [16, 17], and there is clear face validity of this concept considering the proportion of consumers receiving support from rehabilitation services who are not engaged with the available support [17, 58] Additionally, alcohol use has historically been the most common non-tobacco related substance use issue arising in Queensland CCUs and has been anecdotally perceived by staff as detrimental to the rehabilitation process.

A total of 15 potential predictors across three logically determined levels (Level 1 – Consumer/Level 2 – Site/Level 3 – Organisational) will be considered (see Table 4). All predictors identified from the recent literature, with the exception of family involvement, are available. Additional plausible predictors to be considered are ‘rehabilitation engagement’ as assessed through the proxy measure of mode of discharge, functional cognition (via Allen’s Cognitive Levels (ACL) [59]), and substance use (via Alcohol Use Disorders Identification Test (AUDIT) [60]). It is hypothesised that consumers who leave the CCU in a planned manner will be more likely to show improvement than those who do not, and that consumers who experience a positive shift in their stage of recovery will be more likely to show improvement. Additionally, it is expected that lower ratings of alcohol related problems at CCU entry will predict favourable outcomes through rehabilitation engagement. Three additional variables relating to the organisation and site (Staffing model/Site/Length of stay) are planned to be included to exclude moderating effects on the Level 1 predictors. Not all of the available predictors will be used in the final multivariate model, as inclusion of such a large number of variables would risk over-fitting to the relatively small sample size [61]. The stopping rule for inclusion of individual predictors will be defined at the significance level of .05.

**Table 4 Tab4:** Planned variables for inclusion in hierarchical linear regression modelling

Level	Rationale	Construct	Measure/variable name	Type
3 - Organisational	Features with potential impact on consumer experience	Peer support	Staffing model	Dichotomous (Clinical/Integrated)
2 - Site		Site/location	CCU Site	Categorical (Bayside/Coorparoo/Logan)
		Length of Stay	LOS	Continuous
1 - Consumer	Based on previous prediction studies	Demographics	Age	Continuous
			Sex	Dichotomous (Female/Male)
			Education (years)	Continuous
		Primary Diagnosis	Diagnosis	Categorical (Schizophrenia/Schizoaffective Disorder/Other)
		Cognition (functional)	ACL	Scaled
		Medication adherence	LSP-16 (Item 5)	Scaled
		Service utilisation	Psychiatric inpatient bed days	Continuous
		Social function	SFS	Scaled
		Baseline disability	LSP-16 (total)	Scaled
	Novel predictors	Recovery orientation	STORI-30	Ordinal
		Rehabilitation engagement	Mode of discharge	Categorical (Planned/Unplanned - Consumer initiated/Unplanned - CCU initiated)
		Substance use	AUDIT	Ordinal (0-7/8-15/16-19/20+)

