### Analysis

The quantitative analysis will be undertaken in SPSS Version 22 and statistical significance will be assessed at a level of 0.05:The cohort of consumers utilising the services across the three sites will be defined using descriptive statistics. Differences between the sites and staffing models will be examined using t-tests and chi-squared analyses. Assuming comparability of the cohorts is established it is planned that the data from the two integrated staffing model sites will be able to be combined.In order to answer the question of equivalence of the integrated and clinical staffing model for CCUs, differences in the total HoNOS score pre admission and post discharge will be assessed using a t-test or Mann–Whitney U test depending on the normality of the distribution.The question of whether CCU rehabilitation care results in change in specific clinically relevant outcome domains, will be answered through analysis of the secondary outcome measures. It is anticipated that data from the secondary outcome measures will be dichotomised and subjected to Mann–Whitney U analysis with appropriate correction for multiple comparisons.Predictors of change in psychosocial functioning following CCU care will be explored using hierarchical linear regression modelling. The dependent variable is the same as the primary outcome variable for the overall study, mean change in total HoNOS score pre admission and post discharge from CCU care. The independent variables will be entered cumulatively with the organisational (Level 3) variable considered first, followed by the site related (Level 2) variables and then the consumer (Level 1) variables. A hierarchical approach is appropriate given the expectation of inter-correlation between the predictors [68].

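### The predictor regression adjusts for staffing model, site and length of stay but, as described, cannot exclude moderation by them (minor)

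*Protocol article*

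**What the plan says.** The section on planned predictors announces "A total of 15 potential predictors across three logically determined levels". Three of these (staffing model, site, length of stay) sit at the organisational and site levels, and the article says they "are planned to be included to exclude moderating effects on the Level 1 predictors". Table 4, titled "Planned variables for inclusion in hierarchical linear regression modelling", lists the 15 as single variables and contains no product of two variables.

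The quantitative Analysis section gives the order of entry: "The independent variables will be entered cumulatively with the organisational (Level 3) variable considered first", then the site variables, then the consumer variables. Its reason for this structure is "A hierarchical approach is appropriate given the expectation of inter-correlation between the predictors". On selection, the predictors section adds: "The stopping rule for inclusion of individual predictors will be defined at the significance level of .05".

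The same section states directional hypotheses for three consumer predictors: planned discharge, a positive shift in recovery stage, and fewer alcohol problems at entry.

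**The concern.** Moderation means that the effect of a consumer predictor, such as planned discharge, differs by staffing model, site or length of stay. A model of single variables entered in blocks gives each predictor one effect across all levels of the other variables, so every such difference is fixed at zero. The staffing coefficient then asks whether mean HoNOS change differs between the two models. It does not ask whether planned discharge matters more under one of them. The stated purpose is therefore a property that the described analysis does not have.

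What is at stake is how the regression is later read. With the sentence as it stands, a report could say that a predictor holds regardless of staffing model because moderation had been excluded. Nothing in the analysis would support that.

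**Working it through.** **1. Reproduce the article's count.** Table 4 has 1 organisational, 2 site and 12 consumer variables: 1 + 2 + 12 = 15, as stated. None is a product term. The Analysis section adds no interaction step, stratified fit or random slope, and it justifies the hierarchy by correlation among predictors, which concerns overlap and not effect modification.

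**2. What the additive model estimates.** Inputs from the article: minimum sample 40 clinical and 60 integrated (Sample section), significance level 0.05 (Analysis section; two-sided assumed). If a standardised predictor has slope b_C under clinical and b_I under integrated staffing, and is distributed alike in both, the additive slope is about 0.4·b_C + 0.6·b_I. For slopes 0 and 0.5 this is 0.4×0 + 0.6×0.5 = 0.30. For −0.75 and 0.5 it is −0.30 + 0.30 = 0.

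**3. Does any output of that model respond to moderation?** Simulation with 5,000 runs per row and residual SD 1. The article gives no effect sizes, so all slopes and staffing effects are assumptions.

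| Slopes clinical / integrated | Staffing main effect | Staffing term p<.05 | Predictor p<.05 | Mean additive slope | Interaction p<.05, if fitted |
|---|---|---|---|---|---|
| 0.3 / 0.3 | 0 | 4.7% | 82.6% | 0.300 | 5.0% |
| 0 / 0.5 | 0 | 4.9% | 80.2% | 0.301 | 64.6% |
| −0.5 / 0.5 | 0 | 5.5% | 15.8% | 0.098 | 99.5% |
| −0.75 / 0.5 | 0 | 5.4% | 7.8% | 0.000 | 100% |
| 0.3 / 0.3 | 0.6 SD | 82.7% | 82.1% | 0.298 | 4.9% |

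With no staffing main effect, the staffing term stays at its nominal rate (4.7% to 5.6% over all settings tried) however far the slopes differ. With a main effect and equal slopes it is significant in 83% of runs, so significance is no sign of moderation either. Adding staffing moved the predictor's coefficient by more than 0.1 in at most 1.1% of runs. Rows 1 and 2 are nearly the same in every additive-model column, although only row 2 contains moderation.

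**4. What an interaction term could show at this size.**
- Standardised continuous predictor: SE of the slope difference ≈ √(1/40 + 1/60) = 0.204. The 95% half-width is 1.96×0.204 = 0.40, and 80% power needs (1.96 + 0.84)×0.204 ≈ 0.57 SD per SD.
- Planned versus unplanned discharge, 60% planned (assumed): SE ≈ 0.204/√(0.6×0.4) = 0.417, half-width 0.82 SD. Half-widths for other planned shares are 0.80 at 50% and 1.00 at 80%. In 3,000 simulated runs, power was 22% for a 0.5 SD difference and 65% for 1.0 SD.

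A non-significant interaction would therefore not exclude moderate moderation.

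**5. Degrees of freedom.** As coded, mode of discharge has three categories, STORI-30 change three and AUDIT four bands, so staffing interactions with all three would need 2 + 2 + 3 = 7 df. With discharge as planned versus unplanned and the two ordinal variables scored linearly, they need 1 + 1 + 1 = 3.

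**The case against.** The best reply is that one word is wrong and the model is right. The three variables enter before the consumer variables, the hierarchy is justified by inter-correlation, and Table 4's rationale for them is a possible influence on consumer experience. All of that describes covariate adjustment. This stands, and it is why the main remedy is a change of wording. It does not rescue the sentence, because adjustment and exclusion of moderation are different claims.

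A second reply is that the article never says main effects only, and product terms may sit in a fuller plan. That is fair as far as it goes. But the article says that including these variables serves to exclude moderation, and inclusion alone does not do so.

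A reader might infer more: that the study is set to announce absent moderation almost whatever the data show. The article does not support this. It gives no rule for declaring moderation excluded, plans no such statement, and does not list moderation among its research questions. Its regression hypotheses concern predictor effects, not differences in them between models. Nor does it show that the answer to who benefits would be lost, since that aim belongs to the mixed-methods design as a whole and is also pursued by linking interviews to outcome groups. A predictor averaging to about zero and being dropped under the .05 rule needs opposite effects under the two models, which is an extreme case. Under partial moderation (slopes 0 and 0.5) the predictor was significant in 80% of runs and would appear as one blended effect.

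**Conclusion.** The point holds in limited form. The described regression can adjust consumer predictors for staffing model, site and length of stay. It cannot test or exclude moderation by them, and no statement that predictor effects hold regardless of staffing model could rest on it. This follows from the model's structure and needs no assumed effect size. The simulated figures are illustrative: the largest contrasts are worst-case crossovers under assumed slopes, and the discharge figures assume 60% planned exits.

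Severity is minor. The analysis is secondary and exploratory, the primary comparison is untouched, and no erroneous conclusion is actually planned. A further limit is that the clinical model operates at one site, so even a correctly fitted staffing interaction could not be told apart from an effect of that site.

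**What to change.** In the section on planned predictors, replace the phrase on excluding moderation with: *to adjust the Level 1 predictor estimates for these variables*. State that no conclusion about moderation will be drawn from this model.

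If moderation by staffing is of interest, add the following as exploratory:
- Fit staffing model × predictor interactions one at a time, outside the final model and its .05 inclusion rule.
- Limit them to the three predictors with stated hypotheses, at 1 df each: mode of discharge as planned versus unplanned, STORI-30 change scored linearly, and AUDIT band scored linearly.
- Report each difference in effect with its 95% CI, and do not read non-significance as absence of moderation.
- State that staffing cannot be separated from the single clinical site.

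The cost is one phrase and, optionally, three estimates from data already being collected. The intervals will be wide at about 100 consumers, the two kinds of unplanned exit are merged, and linear scoring assumes equal steps between categories.
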